### Sample size

A two-arm, cluster-randomized controlled trial will be used. The sample size was calculated based on the primary outcome. We assumed that a digital crowdsourced intervention will be superior to CDC routine intervention in promoting HIV testing rate among MSM who have not been tested in the past 3 months. Assuming the HIV testing rate is 70% in intervention cities and 50% in the control cities, a total of ten clusters (five in intervention group and five in control group), an intraclass correlation coefficient of 0.02 (usually between 0.01 to 0.03), two-sided *α* = 0.05, power = 0.85, and the loss of follow-up is 30%, the total sample size is 500 men (50 for each cluster). The calculation was made using the software PASS 15.

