### Analysis

The socio-demographic characteristics will be analyzed using descriptive statistics. Comparison in baseline characteristics between the intervention and control arm will be conducted using a chi-squared test adjusted for clustering. The primary outcome of this trial will be the uptake of self-reported HIV testing rate after 12 months. Generalized linear mixed models (GLMM) will be used for the analysis. Intervention status and time will be considered fixed effects, while sites and individual participants with multiple measurements across the four follow-ups will be considered random effects.

The secondary outcomes will include a series of binary variables (continuous variables will be categorized into binary variables), such as number of sexual partners, frequency of anal sex, sex without condoms, frequency of HIV testing (including both facility-based and self-testing), awareness of syphilis status, social network engagement, and others. These will be analyzed similar with the primary outcomes. Furthermore, the interaction effect of intervention between individual level and community level will also be analyzed.

After the 2nd follow-up, we will conduct an interim analysis to evaluate the effectiveness of digital images and videos. After the 4th follow-up, we will also evaluate the effectiveness of digital media and self-test kit using data collected from the 3rd and 4th follow-ups.

The data cleaning, sorting, and analysis will be carried out by team members who do not participate in the randomization and city administration and do not know the treatment allocation. Data analysts were not allowed to modify or delete data. If an outcome is missing for < 15% of participants, analyses will use a complete-case approach. Otherwise, multiple imputation will be used. Participants who miss the follow-up will be included and assumed not achieve the primary and secondary outcomes during the missed follow-up period.

We will also carry out a subgroup analysis based on age (> 30 years old versus ≤ 30 years old) and way of HIV testing (facility-based versus self-testing).

In order to measure contamination, we will conduct per protocol sub analyses to measure whether our results have been affected by contamination.

Results of this study will be distributed to target cities and national stakeholders.

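### The Analysis section gives two incompatible rules for men who miss a follow-up; the sample size fits only one, and the other dilutes the effect and turns unequal drop-out into bias

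*Protocol article*

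**What the plan says.** All references are to the protocol article.

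- **Analysis, threshold rule:** "If an outcome is missing for < 15% of participants, analyses will use a complete-case approach. Otherwise, multiple imputation will be used".
- **Analysis, next sentence:** "Participants who miss the follow-up will be included and assumed not achieve the primary and secondary outcomes during the missed follow-up period". Neither rule is called primary or sensitivity, and nothing says which prevails.
- **Analysis, model:** a generalized linear mixed model with intervention and time as fixed effects, and site and participant as random effects over the four follow-ups.
- **Data collection and management:** all online questions are compulsory. The testing outcome is self-reported.
- **Sample size, effect:** "Assuming the HIV testing rate is 70% in intervention cities and 50% in the control cities". The design inputs are five clusters per arm, a two-sided 5% test and an assumed within-city correlation of 0.02.
- **Sample size, result:** "power = 0.85, and the loss of follow-up is 30%, the total sample size is 500 men (50 for each cluster").

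**The concern.** Two rules could coexist if one covered unanswered items and the other covered missed surveys. Compulsory questions close off that reading, because a missing outcome is then essentially a missed survey. Once each missed survey is scored as not achieved, almost nothing remains to delete or impute. If instead the threshold rule is followed, absent men are not scored as failures. The planned 30% loss is twice the 15% trigger, so on the protocol's own assumption imputation would be called for while the next sentence removes what would be imputed.

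The primary estimate therefore depends on which sentence the analyst follows. Counting absence as not tested makes the outcome a composite of testing and retention. Retention could differ by arm: only the intervention arm receives the fortnightly images, quarterly videos, WeChat groups and self-test kits (Intervention; Follow-up). Extra contact might keep men in or tire them, so the direction is unknown.

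The same sentence covers secondary outcomes. The Analysis section lists sex without condoms and number of partners among these, and for such outcomes it is unclear what not achieving means.

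**Working it through.** **Inputs from Sample size:** 70% versus 50%; 5 clusters per arm; intraclass correlation (ICC) 0.02, usual range 0.01 to 0.03; two-sided alpha 0.05; power 0.85; 30% loss; 50 men per cluster. **Assumed here:** arm-specific retention, because the protocol gives only the overall 30%.

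**1. Reproduce the 500.**
- Individually randomised size per arm, unpooled: n = (1.960 + 1.036)² × (0.70×0.30 + 0.50×0.50) / 0.20² = 103.25.
- With k = 5 clusters per arm: m = n(1 − ICC)/(k − n×ICC) = 103.25×0.98/(5 − 2.065) = 34.5, rounded up to 35 completers per cluster.
- Allowing for loss: 35/0.70 = 50 per cluster, 500 in total. This matches exactly.
- Power check at m = 35: design effect 1 + 34×0.02 = 1.68; SE = √(0.46×1.68/175) = 0.0665; 0.20/0.0665 = 3.01; power 0.85.

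The plan is thus powered on completers at an undiluted 20 points. That is the basis for a complete-case analysis, and roughly the information that multiple imputation has under missing at random. It is not an analysis of all 50 men with absentees scored as untested.

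**2. Absent counted as not tested, 30% loss in both arms.**
- 0.70×0.70 = 0.49 and 0.70×0.50 = 0.35. The difference is 14 points. The risk ratio stays at 1.4; the odds ratio falls from 2.33 to 1.78.
- *ICC kept at 0.02, m = 50:* design effect 1 + 49×0.02 = 1.98; SE = √[(0.49×0.51 + 0.35×0.65)×1.98/250] = 0.0615; 0.14/0.0615 = 2.28; power 0.62.
- *ICC scaled, loss not varying by city:* each city's rate is multiplied by 0.7, so between-city variance is multiplied by 0.49. The ICC becomes 0.02×0.21×0.49/(0.49×0.51) = 0.008 in the intervention arm and 0.02×0.25×0.49/(0.35×0.65) = 0.011 in control. Design effects are 1.40 and 1.53; SE = √[(0.2499×1.40 + 0.2275×1.53)/250] = 0.053; 0.14/0.053 = 2.65; power 0.75.

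Both figures use the large-sample normal method that reproduces the protocol's 500, so the comparison with 0.85 is like for like.

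**3. Unequal loss, no true effect (50% test in each arm).**

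| Assumed retention, intervention vs control | Apparent rates | False difference | Rejection rate, ICC 0.02 | Rejection rate, ICC scaled |
|---|---|---|---|---|
| 80% vs 70% | 40% vs 35% | +5 points | 0.13 (normal), 0.11 (t, 8 df) | 0.15 (normal), 0.13 (t, 8 df) |
| 70% vs 80% | 35% vs 40% | −5 points | same | same |
| 80% vs 60% | 40% vs 30% | +10 points | 0.39 (normal), 0.31 (t, 8 df) | 0.47 (normal), 0.39 (t, 8 df) |

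The nominal rate is 0.05.

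**4. Unequal loss, true 70% versus 50%.** Retention of 80% vs 60% gives 56% vs 30%, a difference of 26 points. Retention of 60% vs 80% gives 42% vs 40%, a difference of 2 points. The rule can inflate the effect or nearly erase it.

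**The case against.** Several stronger readings are tempting, and the document does not support them.

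- **Three conflicting rules.** Complete case and multiple imputation are two branches of one threshold rule and do not conflict. There is one conflict, between that rule and the count-as-failure rule.
- **Count-as-failure overrides the rest.** The protocol states no precedence. That little is left to impute is an inference from the compulsory questions.
- **The sample size fits no missing-data rule.** It fits complete case and, roughly, multiple imputation. Only the count-as-failure rule is out of line with it.
- **Power definitely drops to 0.62.** That figure needs the ICC of 0.02, given for testing, to carry over to being retained and tested. If loss does not vary by city, power is about 0.75. Reading either figure against a t reference would mix in a separate issue, the small number of clusters.
- **Absent men are scored as having had no risky sex.** The coding is not shown. The Trial aims speak of promoting safe behaviour, so not achieving could mean not reaching the favourable state. The direction is unclear, not established.

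Two further points count for the plan. The rule refers to the missed follow-up period, so if uptake is cumulative over surveys, a man who misses some of them can still count as tested, and the shrinkage is smaller. Both arms also get the same payment per survey and the same prize draw, so unequal retention is plausible but not shown. With equal loss no false effect arises.

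These points narrow the size of the problem. They do not remove the contradiction or the sensitivity to unequal loss. An analysis plan that is not shown could choose between the rules, but this text fixes both.

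**Conclusion.** The point holds: two rules for the same participants cannot both be followed, and the one that scores absence as failure departs from the basis of the sample size.

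Its size rests on stated conditions. If the 30% loss applies equally to the 12-month outcome, the expected difference is 14 points instead of 20, and power is about 0.62 to 0.75 against 0.85. The false-positive rate of about 11–15% rests on an assumed 10-point gap in retention and a common testing rate of 50%. The bias can run either way, so the rule cannot be defended as conservative in general. For risk-behaviour outcomes the finding is only that the direction is undefined and could favour absent men.

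This needs correcting before analysis, because the primary estimate turns on it and the repair is cheap.

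**What to change.** Reword the missing-data paragraph in the Analysis section.

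1. Name one primary rule that agrees with the Sample size section. Either of these resolves the conflict:
   - the mixed model already specified, fitted to all observed follow-up records, valid under missing at random (men with no follow-up survey contribute nothing to it, and the text should say so); or
   - multiple imputation by arm, respecting city clustering, with baseline data and earlier follow-ups as predictors.
2. Make missed-equals-not-tested a labelled sensitivity analysis, reported with retention by arm.
3. For each risk-behaviour outcome, state the direction of coding, and do not code absence as the favourable state.

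The cost is one reworded paragraph and one or two extra sensitivity runs. Recruitment and data collection are unaffected.

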### Adverse events and others

We will capture potential unexpected adverse events via spontaneous self-report. We build one WeChat account for each city. Participants can contact us on WeChat so we can capture questions and potential unexpected adverse events. Additionally, some participants will be recruited through local CBOs. The respective CBO leaders can also help us to collect adverse events.

Adverse events will be fully and truly reported on a regular basis to the study PI.

If any modifications to the protocol are required at any point over the course of the trial, these changes will be communicated to relevant parties by email.

## Discussion

Digital crowdsourcing approach has the potential to reach marginalized populations who face multi-level barriers to care, lower the cost of intervention development, aggregate community wisdom, and spur innovation [20, 26, 29, 31]. Several studies and reviews showed that the digital crowdsourcing can improve HIV services for MSM, promote HIV test uptake, and link men to care [19, 24, 29]. It can be a powerful vehicle for increasing HIV testing uptake and making messages more feasible to implement among MSM. The effectiveness of digital crowdsourcing has been examined in few randomized controlled trials, suggesting the need for more rigorous evaluation. We believe that a large-scale, multi-site cluster RCT is needed to evaluate the effectiveness of digital crowdsourcing.


We anticipate that this digital crowdsourcing intervention will increase HIV testing rate and promote safe sexual behaviors among MSM in China. The study outcomes will help to identify the effectiveness of the intervention. The intervention content can be accessed for free to the public. If successful, we hope that the health institutions will utilize this program as a resource and applied to the HIV prevention or to solve other health issues.

## Trial status

This protocol was registered in chictr.org.cn with ID ChiCTR1900024350, identifier http://www.chictr.org.cn/showproj.aspx?proj=36718. Protocol Version: 4.0, date: 27. March 2020. CONSORT Extension for Cluster Trials 2012 Statement was used to guide the writing of this protocol [34]. Recruitment started on 6 August 2019 and finished on 25 January 2020. At the time of this draft, the recruitment has completed. The original study sites included eight cities. Because we found the progress was slow in several cities during the recruitment, especially in the less developed areas, after waiting a reasonable amount of time and discussing with the advisory committee, we decided to add another three cities in our study. City E and City I are two independent cities which are assigned to one block according to the city’s number of HIV-positive in 2018, average GDP in 2017, cumulative number of HIV-positive from 2012 to 2018, and year’s population at the end of 2017. Random numbers were generated using SAS 9.4 software. Finally, City E was assigned to the control arm, City I was assigned to the intervention arm by randomization. City K is a city nearby City J; in this study, City J and City K are in the same cluster considering the number of estimated MSM in both cities is small. In other words, City J and City K were considered as one city in this trial. After adding three cities to the study, we have a total of ten clusters, five in the intervention group and five in the control group. After re-calculating sample size, the total sample size is 500 men (50 to each cluster).

## Data Availability

Data is not applicable now. Materials can be found in Additional file 3. People who are interested in the data can contact us after the trial is completed.

## Abbreviations

AIDS: Acquired immune deficiency syndrome
CBO: Community-based organization
CDC: Chinese Center for Disease Control and Prevention
GLMM: Generalized linear mixed models
HIV: Human immunodeficiency virus
LMIC: Low-income and middle-income countries
MSM: Men who have sex with men
QR code: Quick response code
RCT: Randomized controlled trial
STI: Sexually transmitted infection
UNAIDS: The Joint United Nations Programme on HIV and AIDS
